### Recruitment and randomisation

The patients are recruited from hospitals in the Amsterdam region. Potentially eligible patients are identified through hospital registries, for the 5-years retrospective inclusion, and through treating physicians, for the 2-years prospective inclusion. They are sent a letter signed by their physician informing them of the study and, if initially interested, asking them to complete a brief questionnaire to screen for menopausal symptoms. If they have no further interest in the study, they are asked to complete a postcard indicating reasons for not participating. In case of no response to the questionnaire or the postcard, a reminder is sent two weeks after the first mailing.

Those women who meet criteria for study entry based on their questionnaire responses are contacted by telephone to provide additional information on the study and to confirm their eligibility. In addition, they receive an extensive baseline questionnaire and informed consent form by mail. Computerized randomization takes place after response to both this baseline assessment and the informed consent. Block randomisation is used to ensure that each intervention consists of equally sized groups. In view of the nature of the interventions, blinding of the participants and the researchers is not possible.

During the follow-up period, self-administered questionnaires are sent to the patients at 12 weeks (T1) and 6 months (T2) post-study entry. Upon completion of the study, women assigned to the control group will be given the choice of undergoing either the CBT or physical exercise program.

### Interventions

The CBT and relaxation training consist of 6 weekly group sessions (with 6–8 participants per group) of approximately 1.5 hours duration. It also includes homework assignments (e.g. keeping a daily diary to monitor symptoms and their precipitants). The CBT program is based on the work of Hunter et al. [31] It comprises the following elements: (1) information and advice about symptoms (e.g. hot flushes, night sweats and sexual functioning); (2) monitoring and modifying precipitants; (3) relaxation and stress reduction; (4) cognitive restructuring of unhelpful thoughts, elicited by group discussion; and (5) encouraging helpful behavioral strategies (e.g. pacing activities). The primary focus of the CBT is on hot flushes and night sweats, but other symptoms (e.g. vaginal dryness) and problem areas such as sexuality, body- and self-image, and mood disturbance are also addressed. Relaxation is demonstrated and practiced during each session and an audio CD is provided for practicing at home. A 'booster' session is held approximately 6 weeks following completion of the initial 6 week program. The CBT is delivered by a social worker or psychologist and an assistant, usually an undergraduate psychology student.

The physical exercise program includes 4 individual contacts with a physiotherapist (one in-clinic intake of 90 minutes, two 15-minute telephone contacts, and a final 60-minute in-clinic session). Its core is an individually tailored, home-based and self-directed physical exercise program of 2.5–3 hours per week. During the first, supervised intake session, the exercise program is individually tailored, taking into consideration lifestyle, past and current levels of activity, preferences for types of activities (e.g. walking, cycling, gym exercises, etc.), and any disabilities. Each woman is provided with a heart-rate monitor, and is instructed in its use to achieve a target heart rate (60–80% Karvonen). In weeks 4 and 8, women have a brief telephone contact with the physiotherapist to discuss their experiences with the program and to make modifications, if necessary. Additionally, each week a telephone consultation hour is scheduled during which women can call the physiotherapist to discuss their exercise program, if desired. At the end of the program (week 12) women visit the clinic for a final session, during which advice is given on how best to maintain the level of physical activity (as used in the program) following completion of the program. At this time the data from the heart monitor are downloaded onto a computer.

Women assigned to the combined intervention group (AB) undergo the CBT and physical exercise elements of the program concurrently. To as great an extent as possible, the on-site CBT and in-clinic exercise training sessions are scheduled on the same day.

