### Sample size

The FACT-ES scale, assessing endocrine symptoms [41] is the primary outcome on which sample size calculations are based. Specifically, mean group differences in the FACT-ES scores at 12 weeks and 6 months follow-up, controlling for baseline value, will serve as the primary endpoint of the study. With a total sample of 260 women (65 per group), and under the assumption of no interaction, the study will have 90% power to detect an effect size of 0.4 for the main effects of CBT (n = 130) and physical exercise (n = 130), with the p-value set at 0.05. If the combined effects of CBT and physical exercise are cumulative, or if the effect of CBT varies as a function of exposure to exercise or vice versa, (i.e. there is a significant interaction between CBT and exercise), this number of patients will allow testing each of the 4 cells in the factorial design (group A, B, AB and control group) separately with 80% power to detect an effect size of 0.5, again with p-value set at 0.05. [42]

We will recruit 325 women into the study, to allow for an attrition rate of approximately 20% (i.e. women who discontinue participation in the study entirely, including failure to complete all follow-up questionnaires; those women who discontinue participation in one of the groups but complete the follow-up assessments will be included in the analysis). Thus, 260 women will be available for the primary intention-to-treat analysis.

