### Statistical analyses

Analysis will first be performed to evaluate the comparability of the intervention and control groups at baseline in terms of sociodemographic and clinical characteristics. Student's t-test or appropriate non-parametric statistics will be used, depending on the level of measurement. If, despite the stratified randomization procedures, the groups are found not to be comparable on one or more background variables, those variables will be employed routinely as covariates in subsequent analyses.

Scores for the FACT-ES, the Hot Flush Rating Scale, the BFLUTS, the SAQ, the QLQ-BR23 body image scale, the HADS, and the SF-36 will be calculated according to published scoring algorithms. Between-group differences over time in mean scores will be tested using a two factor (group × time) multivariate analysis of variance with repeated measures on the time factor. Effect sizes will be calculated using standard statistical procedures. All analysis will, to as great an extent as possible, be conducted on an intention-to-treat basis. In addition, we will perform per-protocol analyses based on patients who complete the entire intervention. As indicated previously, the FACT-ES and the Hot Flush Rating Scale will be used as the primary study endpoints, and the remaining measures will be considered as secondary endpoints. For the analysis of these latter variables, appropriate statistical (p-value) adjustments will be made for multiple testing.

Supplementary analyses will be carried out in which data relating to compliance with the program elements is taken into account. Specifically, we will determine whether the level of compliance (based on attendance records, self-report data and, in the case of physical exercise, data stored in the heart rate monitor) is associated significantly with the changes over time in symptom relief, sexuality, body image, psychological distress, and health related quality of life.

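### CBT is given in therapy groups of 6–8, but the stated power and the stated model treat all women as independent; unless the therapy-group correlation is negligible, tests of CBT against non-CBT arms are anti-conservative and their stated power is optimistic

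*Protocol article*

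**What the plan says.** **Delivery of CBT (Interventions).** "The CBT and relaxation training consist of 6 weekly group sessions (with 6–8 participants per group) of approximately 1.5 hours duration". Each group is led by a social worker or psychologist with an assistant, and a booster session follows. One listed component is "cognitive restructuring of unhelpful thoughts, elicited by group discussion", so exchange between participants is part of the treatment.

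**Delivery of exercise (Interventions).** "The physical exercise program includes 4 individual contacts with a physiotherapist"; its core is a home-based programme tailored to each woman. Nothing in it is delivered in groups. Controls are on a waiting list.

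**Power (Sample size).** "With a total sample of 260 women (65 per group), and under the assumption of no interaction", the article claims "90% power to detect an effect size of 0.4 for the main effects of CBT (n = 130) and physical exercise (n = 130"). For the four cells compared separately it claims that they can be tested "separately with 80% power to detect an effect size of 0.5, again with p-value set at 0.05". The only inflation is for attrition of about 20%, from 260 to 325.

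**Analysis (Statistical analyses).** Differences between groups over time "will be tested using a two factor (group × time) multivariate analysis of variance with repeated measures on the time factor". Here group means randomised arm. No term for therapy group is named, and the article does not mention clustering.

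**The concern.** Women who share a leader, an assistant and the same discussions are likely to have more similar outcomes than women who do not. Because this affects two of the four arms, the design is partially nested. The stated calculation and model both assume that each woman is an independent observation.

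With any positive within-group correlation, the sampling variance of a CBT-arm mean is larger than the model assumes. Tests of the CBT main effect and of a CBT arm against a non-CBT arm then reject too often under the null, and their true power is below the independence figure. These tests serve the trial's first hypothesis on the primary outcome.

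**Working it through.** **Inputs from the article**
- Evaluable women: 260, that is 65 per cell and 130 per side of each main effect.
- Effect sizes: 0.4 (main effects) and 0.5 (cells); significance level 0.05. Sidedness is not stated; two-sided fits.
- Therapy-group size 6–8 at delivery; attrition about 20%.

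**Assumed, because the article gives no figure**
- ICC of 0.01 to 0.10, and the same total SD (set to 1) in all arms.
- Analysed women per group (m). Groups form from randomised women, so 325/2 = 162.5 women in groups of 7 make about 23 groups. If 20% are lost evenly, 7 × 0.8 = 5.6 per group are analysed. I show m = 5.6 and m = 7 (no loss within groups).

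**Step 1: reproduce the stated figures under independence**

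Power = Φ(d/SE − 1.96).
- Main effect: SE = √(2/130) = 0.1240; Φ(0.4/0.1240 − 1.96) = 89.7%, against 90% stated.
- Cell: SE = √(2/65) = 0.1754; Φ(0.5/0.1754 − 1.96) = 81.3%, against 80% stated.
- Recruitment: 260/(1 − 0.20) = 325, as stated.

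One-sided versions give 94.3% and 88.6% and do not fit. The match leaves no clustering allowance in the 260.

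**Step 2: inflate the variance on the CBT side only**
- Design effect: DE = 1 + (m − 1) × ICC.
- Main effect: SE = √((DE + 1)/130).
- CBT-only against control: SE = √((DE + 1)/65).
- True type I error of the unadjusted test: 2 × [1 − Φ(1.96 × √(2/(DE + 1)))].

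Example at m = 5.6, ICC 0.05: DE = 1 + 4.6 × 0.05 = 1.23. Main-effect SE = √(2.23/130) = 0.1310, power Φ(0.4/0.1310 − 1.96) = 86.3%. Cell SE = √(2.23/65) = 0.1852, power 77.0%. Type I error 6.3%.

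| m | ICC | DE | CBT main effect, d = 0.4 | CBT-only v control, d = 0.5 | Type I error |
|---|---|---|---|---|---|
| 5.6 | 0.01 | 1.046 | 89.0% | 80.5% | 5.3% |
| 5.6 | 0.05 | 1.230 | 86.3% | 77.0% | 6.3% |
| 5.6 | 0.10 | 1.460 | 82.8% | 72.9% | 7.7% |
| 7 | 0.01 | 1.060 | 88.8% | 80.2% | 5.3% |
| 7 | 0.05 | 1.300 | 85.3% | 75.7% | 6.8% |
| 7 | 0.10 | 1.600 | 80.7% | 70.5% | 8.6% |

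The cell column assumes that each therapy group contains women from one arm. If CBT-only and combined women were mixed evenly, about half of each group (2.8 to 3.5) would be CBT-only. At ICC 0.10, DE for that cell would be 1.18 to 1.25 and power 77.9% to 76.7%. The main-effect column is the same either way, because all 130 women on the CBT side count.

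**Step 3: the other contrasts**
- Exercise-only against control has no therapy groups and stays at 81.3%.
- Combined against CBT-only, the exercise main effect and the interaction depend on whether the two CBT arms share groups.
  - Separate groups: the combined against CBT-only variance is 2 × DE/65. At ICC 0.05, power at d = 0.5 is 72.9% (m = 5.6) or 70.5% (m = 7), with type I error 7.7% or 8.6%. The exercise main effect and the interaction have the same variance ratio, (DE + 1)/2, as the CBT main effect.
  - Evenly shared groups: the group effect cancels, and the combined against CBT-only variance is 2 × (1 − ICC)/65. At ICC 0.05 the type I error is 2 × [1 − Φ(1.96/√0.95)] = 4.4%. For the interaction the ratio is (2 − 0.05)/2 = 0.975, giving 4.7%. Both tests are slightly conservative.

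**The case against.** **The size rests on an assumed ICC.** This stands. At ICC 0.02 and m = 7, DE is 1.12, CBT main-effect power is 87.9% (1.8 points below the reproduced 89.7%) and CBT-only against control is 79.1%. At 0.02 or less the loss is slight.

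**A reader might infer that the interaction and every contrast involving CBT has inflated type I error.** The article does not support that. It says that combined-arm women follow both programmes concurrently, but not whether they attend CBT with CBT-only women. If they do, the comparison of the two CBT arms and the interaction are slightly conservative.

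**A reader might also infer that the stated 90% and 80% are wrong throughout.** They are not: both figures also cover exercise contrasts, and exercise-only against control is untouched.

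**The planned baseline adjustment earns no credit in the stated power.** Correct. If 0.4 and 0.5 are in raw SD units and adjustment shrinks all variance components equally, the baseline correlation needed to offset the loss is √(1 − 2/(1 + DE)). At m = 7 that is about 0.36 for ICC 0.05 and 0.48 for ICC 0.10. So absolute power below 90% or 80% is not proven. But adjustment does not repair the type I error. A group effect that arises during therapy is not removed by a baseline covariate, and the residual ICC may even rise.

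**The article is condensed, and a fuller document may model therapy group.** Possible. The point, however, is not silence: the article names a model and gives power figures, and both assume an independence that its own description of CBT makes doubtful.

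**Conclusion.** The point holds in conditional form. CBT is delivered in groups in two arms only, the stated power contains no allowance for this, and the stated model has no therapy-group term. For any positive ICC the unadjusted tests of the CBT main effect and of CBT against non-CBT arms are anti-conservative; whether that matters in practice depends on an ICC that the article does not give. Across the assumed range the effect runs from trivial (ICC 0.01 to 0.02) to material (about 0.05 and above), as tabulated.

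No single replacement power figure is justified, since it would rest on an ICC chosen by the reader. The analysis defect is the firmer half of the point; the power shortfall could be offset by baseline adjustment. This should be corrected, but it does not invalidate the trial.

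**What to change.** 1. Keep a therapy-group identifier for every woman in the CBT and combined arms. CBT attendance is already recorded (Compliance section); the article does not say whether group membership is. It may be hard to recover later.
2. Analyse the primary outcome with a partially nested mixed model: a random therapy-group effect in the two CBT arms only, women in the other arms as singletons, and small-sample degrees of freedom, as only about 23 groups are expected.
3. State whether CBT-only and combined women attend the same CBT groups, since the other contrasts depend on it.
4. Restate power for the CBT contrasts as conditional on a stated ICC, shown as a range, and say whether the effect sizes are before or after baseline adjustment.

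The cost is one identifier, one model term and a slightly less favourable stated power for CBT. No added patients and no change to the interventions are required.

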### Study measures

The patients' age, education, marital status, work status, weight and height, medication use (including alternative medications or therapies for menopausal complaints or depression) and life style variables (e.g. smoking, physical activity/exercise) are obtained via questionnaire. Clinical information, including date of diagnosis and tumor characteristics, and treatment history (type of surgery, possible breast reconstruction, radiotherapy, chemotherapy, endocrine treatments) are abstracted from the patients' medical records, if possible.

#### Overall levels of menopausal symptoms

The FACT-ES, an 18-item endocrine symptom scale, is used to assess overall levels of menopausal symptoms. [41] It includes both typical (vasomotor symptoms, vaginal dryness) and a-typical symptoms (e.g. weight gain, headaches) of menopause. The FACT-ES has been used among breast cancer patients treated by tamoxifen, [41] and in a sample of Dutch women at increased risk of breast/ovarian cancer who had undergone prophylactic oophorectomy. [43] The scale has shown high levels of reliability (Cronbach's alphas > 0.80 in both studies).

#### Vasomotor symptoms

Hot flushes and night sweats are assessed by the Hot Flush Rating Scale. [44] This 7-item questionnaire assesses the history of hot flushes, their current frequency, severity and duration (in the past week), emotional reactions, perceived disruptiveness, and perceived ability to cope with and control the symptoms. The scale has proven to have good test-retest reliability across a 2–3 week period (r = 0.80). The measure has been used among breast cancer patients treated with tamoxifen. [17]

#### Urinary symptoms

The Bristol Female Lower Urinary Tract Symptoms Questionnaire (BFLUTS) [45] assesses a wide range of urinary symptoms and their impact on sexual function and quality of life. It consists of 5 scales (34 items) assessing incontinence, voiding, filling, sexual function in relation to urinary problems and the impact on health related quality of life. For the purpose of the current study, only the 5-item incontinence scale will be used, including questions on urge, frequency, stress, unpredictable and nocturnal incontinence. The scale has shown to have good reliability (Cronbach's alpha = 0.75).

#### Sexuality

The Sexual Activity Questionnaire (SAQ) [46] is used to assess levels of sexual functioning. This 10-item measure consists of 3 scales: pleasure (desire, enjoyment, satisfaction and current frequency of activities); discomfort (vaginal dryness, pain and discomfort during penetration); and habit (frequency of sexual activity as compared to the usual level). The SAQ has been used in the British Tamoxifen Prevention Trial, [47] several studies of women with breast cancer, [48,49] and of women at increased risk of developing breast/ovarian cancer who had undergone prophylactic oophorectomy. [43] The SAQ has shown to have good reliability (Cronbach's alphas > 0.70).

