### Current study

The present study is systematically evaluating the effectiveness of CBT/relaxation, of physical exercise and of these two program elements combined, in reducing menopausal symptoms, improving sexual functioning, reducing emotional distress, and in improving the health-related quality of life of younger breast cancer patients who experience treatment-induced menopause. In a randomized, controlled, multicenter trial, we are comparing CBT (A), physical exercise (B) and the combination of both interventions (AB) to a 'waiting list' control group.

We hypothesize that women in the CBT group, the physical exercise group or the combined group will report significantly greater reduction in overall levels of menopausal symptoms than patients in the usual care, waiting list control group. Furthermore, we hypothesize that women participating in the combined intervention will report significantly greater reduction in overall levels of menopausal symptoms than those participating in the CBT only or in the exercise only groups. Due to different mechanisms of action, we expect that the combined modalities will be more effective than either modality alone. CBT is expected to lead to significant reductions in menopausal symptoms via cognitive restructuring and stress management, while physical exercise is expected to impact primarily on metabolism of neurotransmitters responsible for thermoregulation. Finally, we hypothesize that women exposed to the interventions (groups A, B and AB) will report significantly more improvement in sexual functioning, body- and self-image, psychological distress, and generic health-related quality of life than those in the control group.

If demonstrated to be effective, the availability of such a structured supportive intervention program will be a welcome addition to standard medical treatment offered to breast cancer patients with treatment-induced menopause. It is anticipated that such a program will have direct benefit in terms of symptom relief and the improvement of patients' health related quality of life.

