## Methods and design

Using a 2 × 2 full-factorial design patients are randomly allocated to one of the four following conditions: CBT, physical exercise, the combination of both interventions or a 'waiting list' control group. The design will allow for testing of the main effect of CBT, the main effect of physical exercise, and the additive or interactive effects of CBT and exercise on menopausal symptoms, the primary outcome measure. Secondary outcomes will include sexual functioning, urinary symptoms, body image and self-image, psychological distress and HRQL. The design of the study and the anticipated flow of the participants are graphically shown in Figure 1. The institutional review boards of all participating hospitals have approved the study. The study is registered at the Netherlands Trial Register (NTR1165) and ClinicalTrials.gov (NCT00582244).

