### Study sample

The study sample will be composed of 325 women, younger than 50 years of age, with histologically confirmed primary breast cancer (stages: T1 – T4, N0 – N1 and M0). All women will have been premenopausal at the time of diagnosis, have completed adjuvant chemotherapy a minimum of 4 months and a maximum of 5 years prior to study entry, and will currently be disease-free. Hormonal therapy can still be ongoing. Potentially eligible women are screened for the presence of at least one of the following 3 menopausal symptoms during the previous week: hot flushes, sweating and/or vaginal dryness. Women are excluded from the study if they lack basic proficiency in Dutch, if they have serious cognitive or psychiatric problems, or serious physical comorbidity that would preclude them from participating in a physical exercise program. Since physical exercise may be contraindicated as a treatment for hot flushes in obese women, [39] patients with a BMI ? 30 are excluded from the study. Patients participating in concurrent studies or rehabilitation programs containing comparable psychosocial interventions are also excluded.

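### In its standard form, the planned MANOVA would test the secondary SAQ discomfort score only in women rateable at all three visits, a group partly defined after randomisation

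*Protocol article*

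**What the plan says.** - **Role of the outcome.** Methods and design lists it as secondary: "Secondary outcomes will include sexual functioning, urinary symptoms, body image and self-image, psychological distress and HRQL". Current study makes it a hypothesis that women in the three intervention groups "will report significantly more improvement in sexual functioning, body- and self-image, psychological distress, and generic health-related quality of life" than controls.
- **Instrument.** Under Sexuality: "This 10-item measure consists of 3 scales: pleasure (desire, enjoyment, satisfaction and current frequency of activities"; the other two scales are "discomfort (vaginal dryness, pain and discomfort during penetration); and habit (frequency of sexual activity as compared to the usual level". Only the discomfort scale mentions penetration.
- **Entry.** Under Study sample, the symptom criterion reads: "screened for the presence of at least one of the following 3 menopausal symptoms during the previous week: hot flushes, sweating and/or vaginal dryness". No criterion concerns sexual activity or having a partner, so hot flushes alone qualify.
- **Intervention.** Under Interventions, the CBT focuses on flushes and sweats, but "other symptoms (e.g. vaginal dryness) and problem areas such as sexuality, body- and self-image, and mood disturbance are also addressed".
- **Analysis.** Under Statistical analyses: "Between-group differences over time in mean scores will be tested using a two factor (group × time) multivariate analysis of variance with repeated measures". Scales are scored by their published rules, and intention to treat applies as far as possible.
- **Who is analysed.** Sample size says that women who stop an intervention but complete the follow-up assessments stay in the analysis. The allowance of about 20% is for women who leave the study entirely or do not return the follow-up questionnaires.

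**The concern.** A woman with no penetrative activity at a visit has no true answer about pain or discomfort during penetration at that visit. The Background section names decreased libido and painful intercourse among the symptoms of the condition, so inactivity is unlikely to be unrelated to the outcome.

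A repeated-measures MANOVA in its standard form drops any woman missing one of the three scores. A woman who resumes activity during the programme lacks a baseline discomfort score, and a woman who stops because of pain lacks a follow-up score. Either could return every questionnaire and still be left out of the discomfort test.

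Activity at 12 weeks and 6 months comes after allocation and may respond to it. The comparison would then no longer be between the groups as randomised. It would also lose women whom the attrition allowance does not cover.

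**Working it through.** **Step 1: the route to the problem.** Discomfort is worded around penetration (Sexuality). Inactive women can enter (Study sample). CBT may change activity (Interventions). The stated model needs complete triples of scores in its standard form (Statistical analyses). The first three are in the text. The complete-triple requirement is a property of the named method, not a sentence in the article.

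**Step 2: the plan's own figure.** Inputs from Sample size: N = 260, main effect 0.4 SD, p-value 0.05 (assumed two-sided). With N split equally,

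power = Φ(0.4 × √(N/4) − 1.96).

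N = 260: 0.4 × √65 = 3.225; 3.225 − 1.96 = 1.265; Φ = 0.897. The stated 90% reproduces, and 260/0.80 = 325 matches the recruitment target. Both figures concern the FACT-ES. The article states no power for the SAQ, so this is a benchmark only.

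**Step 3: loss of unscoreable women.** The article gives no inactivity rate. Assume that 15%, 25% or 35% of women lack a score at one or more visits.

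| Unscoreable | N | 0.4 × √(N/4) | minus 1.96 | Power |
|---|---|---|---|---|
| 0% | 260 | 3.225 | 1.265 | 0.897 |
| 15% | 221 | 2.973 | 1.013 | 0.844 |
| 25% | 195 | 2.793 | 0.833 | 0.798 |
| 35% | 169 | 2.600 | 0.640 | 0.739 |

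These figures precede the multiplicity adjustment planned for secondary measures.

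**Step 4: bias when the programmes have no effect on discomfort.** Take discomfort as standard normal, with correlation ρ between lower discomfort and the tendency to be active, and let a share p be active. Mean discomfort among active women is −ρ × φ(z)/p, where z = Φ⁻¹(1 − p). The values of φ(z)/p are 0.644, 0.570, 0.497, 0.424 and 0.350 for p = 0.60, 0.65, 0.70, 0.75 and 0.80. With ρ assumed to be 0.3 or 0.5:

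- 70% v 70% active: difference 0.
- 65% v 75%: (0.570 − 0.424) × ρ = 0.146 × ρ, or 0.04 to 0.07 SD.
- 60% v 80%: (0.644 − 0.350) × ρ = 0.294 × ρ, or 0.09 to 0.15 SD.

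The group with more active women appears to have more discomfort. This is a single-visit illustration. A simulation under the same assumptions gave the same values to two decimals.

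**The case against.** A reader might infer that sexual functioning as a whole is compared only among active women. The article does not support that. Pleasure includes desire and current frequency, and habit compares frequency with the usual level. On that wording an inactive woman can answer these items. Whether the questionnaire routes her past them is not in the documents.

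A reader might also infer that resumed activity, a real benefit, would be invisible to the trial. That does not follow either, because it can register on the frequency content of both scales. Within discomfort, the wording does not settle whether vaginal dryness depends on penetration, and the FACT-ES also covers vaginal dryness.

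The strongest objection is that no sentence restricts the analysis to active women. The published scoring rules or an analysis plan not shown here may say how inactive women are handled, and a condensed article need not. This stands as far as silence goes, and the restriction is an inference. It does not remove the point, because the article does fix the model. If scoring leaves the value missing, the stated model selects. If scoring instead assigned no discomfort, a woman avoiding intercourse because of pain would score well. Neither is a sound comparison of discomfort in all randomised women.

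It is also fair that the figures rest on assumed rates, that bias under no effect vanishes if activity is equal by group, and that the primary endpoints are untouched.

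**Conclusion.** The point holds for the SAQ discomfort scale alone. Followed as written and in its standard form, the MANOVA would test discomfort in women rateable at baseline, 12 weeks and 6 months. That is in tension with the intention-to-treat aim and with keeping women who complete follow-up in the analysis.

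The size cannot be fixed from the article. On the assumed 15% to 35% unscoreable, power for 0.4 SD falls from about 90% to between 84% and 74%, on a benchmark set for another scale. Bias under no effect is zero with equal activity. It reaches about 0.15 SD only with a gap as wide as 60% v 80% and a correlation of 0.5. Severity is minor: one subscale of one secondary outcome.

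**What to change.** In Statistical analyses:

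1. Analyse the SAQ discomfort score with a likelihood-based repeated-measures model that uses every available visit, in place of a MANOVA needing all three scores.
2. Label the result as conditional on being sexually active at that visit. The model recovers women with partial data, but it does not undo the selection.
3. Report the share of women with a rateable discomfort score by group and visit, so that readers can judge whether activity differs between groups.
4. Add a comparison of sexual activity in all randomised women, using the activity or frequency item that the SAQ already collects.

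The cost is a few sentences, a change of model for one scale and one more secondary test in the multiplicity adjustment. On the article's description of the SAQ, no new data collection is needed.
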